**4.4.5 Follow-up of excluded patients**

Excluded patients from the study remain patients of the University Hospital Aachen and will be treated according to the medical evidence and clinical practice by the attending physicians. The Department of Anesthesiology is 24 hours available by the patient, if the patient is transferred to a special institution. The contact information will be provided to the patient.

It will be recommended to each patient, who withdraws his study-participation, to participate on a final examination.

**5 Individual course of study**

**5.1 Verification of the inclusion- and exclusion criteria**

Verification of the inclusion- and exclusion criteria of potential study-patients (screening) will be conducted according to a predefined checklist: All patients meeting the inclusion criteria: Suspected renal carcinoma limited to one kidney, planned PN and age of ≥18 years will already be informed by the colleagues of the Urology Department. An investigator will visit them if they are interested in study participation. The investigator will inform the patients about the individual risk and benefit of this study and evaluate the exclusion criteria. The patients will receive a patient information and ample of time for their decision to participate in this study. A screening log will be kept, where all eligible patients have to be documented. The enrolled patients will additionally be documented in this screening log. If a patient is not enrolled in this study, then at least 1 exclusion criterion has to be documented. Within the verification of the inclusion / exclusion criteria, the investigator has to document if the patient has participated in another clinical trial within the prior 30 days. The patient will be informed that he is not allowed to participate in further clinical trials, as this bears unpredictable risks for the patient.

**5.2 Patient information**

Each potentially eligible patient has to be informed about the study aims, the voluntariness of participation, and the possibility of withdrawal without reasons, the pseudonymized utilization and publication of the results, and the risks and possible complications. The patients will be informed verbally by the investigator and written by the patient information. After provision of ample time, the patient will be requested to sign and date two informed consent forms. One form will be provided together with the patient information to the patient. The other form will be filed in the investigator site file.

**5.3 Visits**

All patients will undergo a maximum of 11 visits. Visits 0 and 2-10 will be performed in a blinded manner by investigator I. Only investigator II and the study nurse will perform the intraoperative visit un-blinded, due to the special kind of Xe anesthesia administration.

**5.3.1 Visit 0 (Baseline visit)**

Investigator I will perform the baseline visit, after written informed consent. This visit includes the patient medical history and clinical investigation for detection of exclusion criteria. He will assess demographic data (gender, height, weight, age, ASA-status and other), vital function (heart rate, blood pressure, oxygen saturation with air), the central laboratory data (blood cell count, coagulation variables, urea in serum, transaminases, creatine kinases) and the preoperative GFR (estimated by cystatin C in serum) and the creatinine in serum. Additionally, a serum (for MIF determination) and urine sample for additional analyses will be obtained. Data will be documented in a paper-based case report form (CRF). Patients will not be enrolled; if there are exclusion criteria, but they will receive a screening number kept in a file in a cabinet. If there are no exclusion criteria, they will receive a study patient number. A treatment is assigned to each study number already before study start and concealed in an opaque sealed envelope.

**5.3.2 Visit 1 (Surgery day)**

Investigator II will open the randomization envelope shortly before anesthesia induction. Only the respective intraoperative investigator and the study nurse, who collects the intraoperative data, will have access to this treatment allocation. After application of the standard monitoring, the patients will receive a thoracic epidural catheter against postoperative pain.

Anesthesia induction: Both groups ( Xe and control) will receive propofol 1.5-2 mg kg^-1^ and sufentanil 0.2 µg kg^-1^; muscle relaxation will be induced by 0.6 mg kg^-1^ rocuronium.

Maintenance of anesthesia:

Patients in the Xe group will receive general anesthesia with 60% inspiratory Xe/ 40% O_2_, patients in the control group will receive 1.2 % isoflurane end-expiratory in mixed air with 40% O_2_; both groups will receive titrated sufentanil according to the clinical need.

Surgery:

- Mean arterial pressure (MAD) < 65mmHg; Prevention of additional impairment of renal function, by insufficient perfusion. Therefore, the MAD has to be kept continuously > 65mmHg, if necessary with titrated norepinephrine.
- Surgery will be performed according to the SOP of the Department of Urology.
- Assessment of the anesthesia- and safety data every 5 minutes, urine output every hour and the total urine output at the end of anesthesia.
- Incision-suture time, intraoperative blood loss, warm ischemia time corresponding to the tumor resection time and the anesthetic exposition until the beginning of the tumor resection time and after the end of this time (defined by the termination of the tumor ground-treatment), will be assessed in collaboration with the surgeons.
- Resected tumor tissue will be transferred to the Institute of Pathology, where the crop margins will be analyzed rapidly with regard to tumor-freedom. The tumor size, histology by immunochemistry, and optionally the activation of HIF 1α in the in the healthy surrounding tissue will be assessed in addition.
- 5 minutes after the end of ischemia time = termination of the tumor ground-treatment, we will assess macrophage migration-inhibiting factor (MIF) in serum.

Post-anesthesia-care unit (PACU):

- Blood pressure and heart rate will be assessed every 15 minutes and the pulse oxymetry will be measured continuously.
- A further serum sample for MIF measurement will be drawn in PACU

Investigator II will document all assessed data in the paper-based CRF of the respective patient. Follow-up during the hospital stay will last a maximum of seven postoperative days. Urine output will be assessed every 6 hours after surgery via urine catheter. The total urine output will be assessed in the second postoperative day. Urine samples will be collected on the first and second, as well as the seventh postoperative day for optional additional analyses (KIM-1 or NGAL by ELISA). Blood samples will be drawn each morning from the first until the discharge day or maximum 7^th^ postoperative day. Furthermore, the investigator will measure vital function (blood pressure, heart rate, oxygen saturation) daily. Cystatin C will be determined from the blood samples and the GFR will be calculated using cystatin C. Furthermore, the secondary blood outcome variables (creatinine, blood cell count, coagulation, urea in serum, transaminases and creatine kinase) will be determined in the blood samples. A further blood sample will be drawn on the first postoperative day for MIF determination in serum. The investigator will value and document laboratory variables and the amount of urine output in the respective CRF. In addition, the investigator will determine an acute renal failure according to the AKIN criteria [34] on the first and second postoperative day. In-hospital study participation is terminated after physical examination on the discharge day or maximum the 7^th^ postoperative day. We will try to obtain the GFR and creatinine value after 3-6 months postoperative by contacting of the family physician or attending urologist.

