**3.2 Randomization**

The randomization sequence will be generated computer-based by an independent biometrician. Patients will be randomly allocated according to a computer-based algorithm into the two groups Xe or control. Allocation concealment will be achieved by sequentially numbered, sealed opaque numbered envelopes, which will be kept safe until randomization of the single patients. Patients will be enrolled and pseudonymized with sequential increasing numbers by an investigator after obtaining written informed consent. All data will be collected under this pseudonymized number and only the biometrician and the monitor will have access to the randomization sequence, which includes the allocated treatment (Xe or control). The patients, the outcome-assessing investigator and the surgeon will be blinded (the ventilator will be the same for all patients to prevent accidental un-blinding). Only the second investigator, who performs the anesthesia and the intraoperative data assessing study-nurse, cannot be blinded.

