**4.2 Exclusion criteria**

1. Patients with a chronic kidney disease (CKD), and a pre-operative glomerular filtration rate (GFR) < 60 ml min^-1^ 1.73^-1^ m^-2^
2. American Society of Anesthesiologists (ASA) status > III
3. Known contraindication and hypersensitivity to propofol, sufentanil, Xe, Iso or rocuronium
4. Severe pre-existing cardiac disease (New York Heart Association-Classification (NYHA)<III), acute coronary syndrome during the past 24 hours, hemodynamic instability or requirement of catecholamines
5. Severe respiratory disease (Forced expiratory volume in one second/ forced vital capacity (FeV1/FVC)<70% and FeV1<30%), severe respiratory insufficiency with a partial pressure of oxygen in arterial blood (PaO_2_)<60mmHg, or home oxygen therapy
6. Severe neurological disease
7. Increased intracranial pressure
8. Risk for malignant hyperthermia
9. Pregnant or breast-feeding woman
10. Legally incompetent patients
11. Refusal of consent
12. Concurrent participation in other interventional studies in the last 30 days
13. Language and communication difficulties during study information
14. People who are institutionalized by court or administrative order
15. Subjects with dependent/ employment relationship to the sponsor or the investigator

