**4.4 Patient exclusion criteria and procedure**

**4.4.1 Reasons for premature study-exclusion and termination of the investigational product administration**

- Patient safety has the first priority. A patient will be excluded before intervention, if an exclusion criterion appears after patient inclusion- but before intervention- (e.g. change of the surgical technique, acute patient deterioration, etc.). Patient data will receive a screening number and will be stored in a locker.
- A retrospectively noticed deviation from the inclusion or exclusion criteria (after the beginning of the intervention) will induce a study drop out. Depending on the time-point, the patient will receive a standard anesthesia and the data management will excluded the patient.
- Consent withdrawal: Patients can withdraw whenever they want. All collected data until the withdrawal time-point as well as the randomization group have to be filed. The patient has to be informed, that already collected data will be used further on.
- Severe adverse events (SAE) and suspected severe adverse reactions (SUSAR), which prohibit further study conduction.
- Adverse events (AE) and adverse reactions (AR), which seem to be hazardous for the physical and psychological health of the patients, as evaluated by the principle investigator.
- Technical difficulties and required modifications of the investigational product administration device.

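### Exclusion with refiling as a screening case stays open after the unblinded anesthetist has opened the randomization envelope

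*Protocol*

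**What the plan says.** **When the allocation becomes known, and to whom.** Protocol 5.3.2: "Investigator II will open the randomization envelope shortly before anesthesia induction". The next sentence reads: "Only the respective intraoperative investigator and the study nurse, who collects the intraoperative data, will have access to this treatment allocation". Section 3.2 confirms the role: "Only the second investigator, who performs the anesthesia and the intraoperative data assessing study-nurse, cannot be blinded".

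**How long exclusion stays open.** Protocol 4.4.1: "A patient will be excluded before intervention, if an exclusion criterion appears after patient inclusion- but before intervention". The examples given there are "e.g. change of the surgical technique, acute patient deterioration, etc". One exclusion criterion in 4.2 that can arise on the day of surgery is "hemodynamic instability or requirement of catecholamines".

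**What happens to the excluded patient.** Protocol 4.4.1 continues: "Patient data will receive a screening number and will be stored in a locker". Section 5.3.1 uses the same label for people found ineligible at visit 0, who are not enrolled.

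**Related rules.**
- Section 4.1 equates the length of the intervention with that of the anesthesia.
- Section 5.3.1 ties a treatment to each study number before the study starts and conceals it in the envelope.
- Section 4.4.3 has the reason and time of any exclusion entered on a dedicated CRF sheet.
- Section 4.4.4 replaces patients excluded after randomization.
- Section 9.2 analyzes every randomized patient, and 9.3 makes the primary analysis intention-to-treat.

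**The concern.** Concealment works only if nobody who knows the arm can still decide whether the patient belongs in the trial. The sealed envelopes protect the decision at visit 0. They do not protect a decision taken between opening the envelope and starting the anesthesia, because the cut-off in 4.4.1 is the intervention and not the opening.

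Two things are at stake. A borderline patient might be kept in one arm and excluded in the other, so that the arms are no longer comparable at baseline. And the excluded patient would be filed like someone never enrolled and then replaced, although a treatment had been allocated and disclosed. If 4.4.1 is followed as written, that patient leaves the very set that the intention-to-treat analysis is meant to protect.

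**Working it through.** The plan gives no figure for this point, so the check is mainly a comparison of sections.

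**1. Is there an interval in which the arm is known and exclusion is still open?** The envelope is opened before induction (5.3.2). The intervention is the anesthesia (4.1). Exclusion under 4.4.1 runs until the intervention. Opening therefore comes before the cut-off, and the interval exists. It is short, since the opening is close to induction.

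**2. Can a reason for exclusion arise in it?** Yes. Section 4.4.1 names acute deterioration and leaves the list open. Hemodynamic instability is a criterion in 4.2 that can appear in the anesthesia room.

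**3. Is the decision reserved for someone blinded, or is eligibility confirmed before opening?** No section says either.

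**4. Has the patient been randomized by then?** The protocol does not define the moment. Section 3.2 keeps the envelopes safe until the individual patient is randomized, which points to opening. Section 5.3.1 ties the treatment to the study number given at visit 0, which points to an earlier moment. On both readings a patient whose envelope is open has been randomized. A screening number for that patient is then inconsistent with 9.2.

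**5. Could judgment differ by arm?** Section 1.2 describes xenon as hemodynamically favorable and says that other anesthetics, isoflurane included, usually bring low pressures and a need for catecholamines. An anesthetist who holds that view and knows the arm could judge the same unstable patient differently. This is a possible mechanism. Nothing shows that it would operate.

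**6. Illustration of size, on assumptions not in the protocol.** There is no true effect and there are 25 patients per group (9.1). A risk judgment has correlation ρ with the GFR decline. The k xenon patients with the highest judged risk are removed and replaced at random. The test is a two-sided t-test, with 20,000 runs.

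| k removed | ρ | Shift in mean decline, xenon minus control (SD) | p < 0.05 | p < 0.20 |
|---|---|---|---|---|
| 0 | 0.3 | 0.00 | 5.1% | 20.0% |
| 0 | 0.5 | 0.00 | 5.0% | 20.0% |
| 1 | 0.3 | −0.02 | 5.0% | 19.9% |
| 1 | 0.5 | −0.04 | 5.5% | 20.9% |
| 2 | 0.3 | −0.04 | 5.3% | 20.3% |
| 2 | 0.5 | −0.07 | 6.0% | 22.0% |
| 3 | 0.3 | −0.06 | 5.0% | 20.7% |
| 3 | 0.5 | −0.09 | 6.6% | 22.8% |

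The simulation error is about √(0.05 × 0.95 / 20,000) = 0.15 percentage points at the 5% level and √(0.20 × 0.80 / 20,000) = 0.28 points at the 20% level. The 20% column matters because 9.1 treats p-values below 20% as positive signals. The set-up is adverse by construction: removal is deliberate, always of the worst risks and only in the xenon arm. It also uses a t-test and not the baseline-adjusted analysis of 9.3.

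**The case against.** The best defense is that the interval lasts minutes, the exclusion criteria are the same for both arms, and the analysis rules already cover the case. Much of this stands, and it rules out several stronger readings that a reader might infer.

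- **That the unblinded anesthetist makes the decision.** No section names who decides. A change of surgical technique would come from the surgeon, who is blinded under 3.2. The protocol permits an exclusion with the arm known; it does not prescribe one.
- **That the epidural falls inside the interval.** After the sentences on the envelope, 5.3.2 says: "After application of the standard monitoring, the patients will receive a thoracic epidural catheter against postoperative pain". That is sentence order and not a stated sequence. Trouble with the catheter is not an exclusion criterion either.
- **That the two gases impose different practical limits on eligibility.** Sections 3.2, 3.4.2 and 6.2 give both arms the same ventilator, so equipment offers no reason for arm-specific selection.
- **That such cases vanish from the record.** Section 4.4.3 requires the reason and time of exclusion, 5.1 enters enrolled patients in the screening log as well, and the envelopes are numbered in sequence. An opened envelope without an analyzed patient would show.
- **That intention-to-treat cannot help.** It can, if the patient still counts as randomized.

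The last point is where the defense stops short. Sections 9.2 and 9.3 protect only patients who remain in the randomized set, whereas 4.4.1 files this patient as a screening case and 4.4.4 brings in a replacement. The protocol does not say which rule prevails. An analysis plan could settle the set, but it could not recover GFR values that were never collected because the patient had been refiled.

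**Conclusion.** The point holds as a gap in the conduct rules. Between opening the envelope and starting the anesthesia, a patient can be excluded with the allocation known and refiled as if never enrolled. This conflicts with the analysis of all randomized patients in 9.2, and replacement under 4.4.4 compounds it.

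The bias is probably small, and its size cannot be derived from the protocol. With 1 to 3 of 25 xenon patients selectively replaced and ρ between 0.3 and 0.5, the illustration gives an apparent benefit of 0.02 to 0.09 SD, a two-sided 5% error rate of 5.0% to 6.6%, and a 20% signal rate of about 20% to 23%. The number of such exclusions and ρ are assumptions; the direction would follow whatever selection took place.

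The conclusion rests on reading the intervention as the anesthesia, as 4.1 does, and on 4.4.1 being applied as written. It does not depend on the timing of the epidural or on any claim that selection will in fact occur. The case would be traceable, so this is a rule to tighten and no sign of concealed manipulation.

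**What to change.** **Section 5.3.2.** Require a final eligibility confirmation, documented with date and time, before the envelope is opened. Record the time of opening, and define opening as the moment of randomization. Because the confirmation precedes opening, it does not matter for concealment who signs it.

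**Section 4.4.1.** Limit the screening-number route to exclusions made before the envelope is opened. A patient excluded after opening may still be taken off study treatment as the protocol already provides. That patient keeps the study number, is followed for GFR where consent allows, and stays in the intention-to-treat set and the patient flow.

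**Section 4.4.4.** State that a replacement is added to such a patient and does not take that patient's place in the analysis set, so that the section agrees with 9.2.

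**Cost.** A few sentences, one line with a time stamp on the envelope or CRF, and GFR follow-up for what should be very few patients. Where values are missing, the imputation already foreseen in 9.3 applies. No drug, dose or treatment rule changes.

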**5.3.3 Visit 2 (Surgery day, postoperative)**

- The urine output will be assessed every 6 hours after surgery via urine catheter.
- Furthermore, we will assess and document AEs and SAEs.

**5.3.4 Visit 3 (1^st^ postoperative day)**

- The urine output will be assessed every 6 hours after surgery via urine catheter until the second postoperative day.
- Investigator I will measure the patients` vital data (blood pressure, heart rate, oxygen saturation) and draw blood samples in the morning. We will need the following laboratory data: Cystatin C will be determined from the blood samples for calculation of GFR using cystatin C. Furthermore, the secondary blood outcome variables (creatinine, blood cell count, coagulation, urea in serum, transaminases and creatine kinase) will be determined in the blood samples.
- The last blood sample for MIF determination in serum will be drawn in addition.
- One urine sample will be drawn for optional KIM-1 or NGAL determination.
- The investigator will value and document laboratory variables and the amount of urine output in the respective CRF. The investigator will determine an acute renal failure according to the AKIN criteria [34] on the first and second postoperative day.
- Evaluation and documentation of AEs and SAEs.

**5.3.4 Visit 4-8 (2^nd^-6^th^ postoperative day)**

- Investigator I will measure the patients` vital data (blood pressure, heart rate, oxygen saturation) and draw blood samples in the morning.
- The total urine output will be measured on the 2^nd^ postoperative day
- One urine sample will be drawn.
- Laboratory data determination, please refer to 5.3.4
- The investigator will value and document laboratory variables and the amount of urine output in the respective CRF.
- The investigator will determine an acute renal failure according to the AKIN criteria [34] on second postoperative day.
- Evaluation and documentation of AEs and SAEs.

**5.3.6 Visit 9 (7^th^ postoperative day or discharge day/ end of study, respectively)**

- The investigator I will perform physical examination, measurement of the patients` vital data, blood sample drawing (laboratory variables, see 5.3.4). The in-hospital study participation ends maximum at the 7^th^ postoperative day.
- Evaluation and documentation of AEs and SAEs.

**5.3.7 Visit 10 (3-6 months postoperative)**

- Contacting of the family physician or attending urologist, to obtain the GFR and creatinine value, which was probably measured during the clinical postoperative routine.

**6 Investigational products**

**6.1 Name**

- Xenon 100% (v/v)
- Isoflurane

**6.2 Administration**

Both Xe anesthesia as well as control anesthesia will be administrated by a special closed circuit (Felix Dual, Taema, ALMS, France).

**6.3 Packaging, labeling and storage of the investigational drugs**

Medical Xe (LenoXe®, 100% v/v, Air Liquide) will be provided and labeled according to the European regulations in steel cylinders. It will be stored at room temperature, protected from light and in a cool place. Isoflurane (250ml, Abbott) will be provided in specific bottles and stored at 4 degrees Celsius in a light protected box. It will be vaporized by specific refillable vapors.

